**Discussion:**

This trial will implement a high-quality methodology and may provide evidence for the efficacy, safety, and specificity of auricular acupuncture as a treatment for pregnant women with LBPGP.

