### Hypothesis and study goals

Our clinical hypothesis is that acupuncture applied via pressure needles inserted in the auricle (VAAc), associated with standard obstetric care (SOC), can reduce the pain experienced by pregnant women in the lower back and/or the posterior pelvic girdle, to a greater extent than is achieved by SOC alone in the field of primary health care. Additionally, the application of this technique improves patients’ functional status and health-related quality of life, and moderates the consumption of drugs used in conventional therapy, thus reducing the associated iatrogenic effects without provoking significant iatrogenesis in itself. Secondly, VAAc applied together with SOC has specific effects, achieving a greater reduction in the LBPGP suffered by pregnant women than that achieved with the application of pressure needles at non-specific pressure points (NSAAc) or with placebo needles at non-specific points (PAAc).

The main aim of this study is to evaluate the efficacy achieved in terms of reduction in pain intensity (0 to 100 mm visual analogue scale) at 2 weeks after starting treatment. Our secondary aims are: i) to evaluate the efficacy in terms of improved functional status with respect to LBPGP (according to the Roland-Morris disability questionnaire) at two weeks after starting treatment; ii) to evaluate the efficacy in terms of improved health-related quality of life (SF12) at two weeks after starting treatment; iii) to evaluate the efficacy in terms of improvement perceived by the patient with LBPGP at two weeks after starting treatment; iv) to evaluate the impact on temporary occupational incapacity of pregnant women with LBPGP; v) to evaluate the efficacy in terms of reduced consumption of analgesic medication at 2 weeks after starting treatment; vi) to evaluate the presence of LBPGP at 12 weeks postpartum; vii) to evaluate the presence of LBPGP at 48 weeks postpartum; and viii) to estimate the placebo effect and the specific and non-specific effects of VAAc, NSAAc, and PAAc.

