### Study scope and subjects

The study population will be composed of pregnant women (24 to 36 weeks’ gestation), aged 17 years or more, referred by their family physicians from the 21 primary care centres participating in the study, belonging to the Andalusian Public Health System and located in the provinces of Seville and Málaga, diagnosed with pregnancy-related LBPGP and who have not previously received auricular acupuncture. Women with LBPGP that began before the pregnancy, or presenting any of the ‘red flags’, which would require examination to rule out the possible presence of LBPGP secondary to inflammatory, infectious, traumatic, neoplastic, or degenerative processes, together with women receiving anticoagulant treatment or presenting dermatitis of the auricle, will be excluded from the study.

The women will be given the following information: “*This study is being conducted to compare the effects of standard obstetric care either alone or in conjunction with one of three types of stimulation of the ear (auricular acupuncture). One of these is similar to traditional Chinese auricular acupuncture, while the others do not follow these principles. One is a placebo intervention, but all have been associated with positive outcomes in various clinical studies*”. The women will also be informed of the potential risks associated with different types of auricular acupuncture (infection, pain at the puncture site, fainting, bruising) and that they may terminate their participation in the study at any time without any penalty or loss of the benefits to which they are entitled. All study participants must sign the informed consent form.

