#### Placebo acupuncture (PAAc)

The devices used in the placebo group will be supplied by Seirin (Pyonex Placebo, Seirin, Shizuoka, Japan) and by 3B Scientific (Spain). They will be identical to those used in the VAAc group, but without the needle [34] (Figure 2), and will be applied at the same non-specific points as for the NSAAc group.

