### Variables

The primary outcome will be the reduction in pain intensity, according to the visual analogue scale (iVAS), at 2 weeks after the start of treatment. The secondary outcomes will be functional status with respect to LBPGP (according to the Roland-Morris disability questionnaire) and health-related quality of life (SF12) at 2 weeks after the start of treatment, iVAS score at 12 and 48 weeks postpartum, presence of temporary occupational incapacity, reduction in the consumption of analgesic medication at 2 weeks, and presence of pain at 12 and 48 weeks postpartum.

The obstetric data, based on the patient’s health record, will consist of gestational age (weeks), number of previous pregnancies, number of children, previous caesarean sections, and whether epidural anaesthesia was required. The personal data compiled by the midwives participating in the study will be patient’s age (years), weight before pregnancy and present weight (kg), height (cm), body mass index before pregnancy (calculated as weight/height^2^), educational level (none, primary education, secondary education, high school, university), and employment status (employed, non-employed, type of work and, where appropriate, the reasons for not working). In addition, any previous pregnancy-related LBPGP will be recorded. If the patient is temporarily unable to work, the days elapsed since this condition began will be noted, and its follow-up at T2, T3, and T4. The data form will also record the consumption of healthcare resources since the beginning of the LBPGP (number of times treated by the family doctor, number of times emergency treatment needed at the health centre or hospital, number of visits to a medical specialist, private doctor, company doctor, or non-conventional healthcare professional).

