We will also evaluate the consumption of analgesic medication, whether or not prescribed by the patient’s doctor, both at the time of randomisation (T0) and at final assessment (T2), according to a 4-point Likert scale of 0–3: (0) = none, (1) = less than the usual dose, (2) = usual daily dose, and (3) = greater than the usual dose. We will also record the names of the medications taken and the daily dose in each case.

The Treatment Credibility Scale [43] will be used to evaluate patients’ expectations and the credibility of the treatments provided in the study. The original Borkovec and Nau scale [44] with four items will be applied, assessing the following questions on a continuous VAS of 0 to 10 (0 to 10, from totally disagree to totally agree): (1) = Are you confident that this treatment can alleviate your pain? (2) = Does it seem a logical treatment? (3) = Would you recommend this treatment to a friend or family member who was suffering the same problem? (4) = Do you think this treatment would be an option for treating other problems? Questions 1 and 2 will be assessed after the first treatment session, and questions 3 and 4, after 2 weeks.

After the treatment has concluded, the blinding of the patients’ allocation to one of the two auricular acupuncture groups (real or placebo) will be verified by the following dichotomous question: Do you think you were assigned to the real auricular acupuncture group or to the placebo group?

During the study, side effects and possible adverse reactions resulting from the treatment will be recorded.

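### Recording adverse events only when attributed to treatment leaves no all-cause event rate in any arm and no comparable rate in standard care to support the safety statements

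*Protocol article*

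**What the plan says.** Near its end, the Variables section states that during the study "side effects and possible adverse reactions resulting from the treatment will be recorded". No other sentence in the article governs safety data.

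Two places make a safety statement. The hypothesis (Hypothesis and study goals) expects the technique to lower drug consumption, "thus reducing the associated iatrogenic effects without provoking significant iatrogenesis in itself". The Discussion paragraph of the Abstract says the trial "may provide evidence for the efficacy, safety, and specificity of auricular acupuncture". Safety is not among the eight secondary aims, the outcomes listed under Variables, or the comparisons under Statistical analysis.

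The obstetric data under Variables are gestational age, "number of previous pregnancies, number of children, previous caesarean sections, and whether epidural anaesthesia was required". Gestation at delivery, mode of delivery and birth weight are not listed.

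On staff, the midwife is told the allocation (Randomisation and blinding procedures), is trained in the technique (Treatment) and carries out the assessments from T0 to T4 (Data sourcing and compilation). The main Discussion accepts that the therapist cannot be blinded. It also says that whoever gives the treatment takes no part in assessing the outcome.

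**The concern.** A safety comparison needs events counted in the same way in every arm, with causality judged afterwards. Here causality is the entry test. An event that nobody connects with the treatment leaves no trace in the adverse-event data, whichever arm it occurs in. The background rate is then missing, and that is the rate needed to judge whether an excess exists.

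This matters most for VAAc against SOC, the contrast that carries the hypothesis, the sample size and the main analysis. The hypothesis is also one of net harm: fewer drug effects, with no significant harm added. If the person attributing events knows the arm, the count can also reflect expectation. A reassuring safety statement could then owe something to the recording rule as well as to the treatment.

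**Working it through.** **1. The plan's own figure.** Inputs from Sample size and Statistical analysis: difference 20 mm, SD 25 mm, two-sided alpha 0.01, power 0.90, 10% loss.
- n per group = 2 × [25 × (2.576 + 1.282) / 20]² = 46.5, rounded up to 47.
- 47 / 0.90 = 52.2, rounded up to 53; 4 × 53 = 212.

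The stated 47, 53 and 212 reproduce. They are sized for pain, and no safety figure is stated.

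**2. What the recording rule yields, by comparison.** The sentence does not say whether *treatment* means the device alone or also standard care, so both readings are followed.
- *Device arms against each other (either reading).* PAAc devices: "They will be identical to those used in the VAAc group, but without the needle". NSAAc uses the same needles at other points. Patients in all three arms are blinded. Attributed reactions can be compared, and NSAAc against PAAc isolates the needle at the same points.
- *VAAc against SOC, treatment = device.* SOC has no device, so it has no recordable reaction. Its zero comes from the definition.
- *VAAc against SOC, treatment includes standard care.* SOC can contribute reactions attributed to exercises or paracetamol. VAAc contributes these plus device reactions. A faint that nobody links to treatment is still missed in both arms, while the same faint is easier to attribute in a woman wearing needles. The two counts do not measure the same thing.
- *All-cause events.* Not obtained in any arm under either reading.

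**3. Who attributes.** Randomisation and blinding procedures, Treatment, and Data sourcing and compilation together point to the midwife, who knows the arm. The main Discussion says that the treating professional does not assess the outcome. Its other safeguard, self-administered questionnaires, covers the primary and many secondary outcomes; no such form is described for adverse events. The likely attributor is thus unblinded, but this is an inference.

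**4. What 53 women per arm can exclude.** With zero events in n women:
- one-sided 95% upper limit = 1 − 0.05^(1/53) = 0.055, or 5.5%;
- two-sided exact upper limit = 1 − 0.025^(1/53) = 0.067, or 6.7%;
- chance of seeing at least one event = 1 − (1 − p)^53, which is 41% at p = 1% and 93% at p = 5%.

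**5. What full recording could detect.** The article gives no event rates, so these are assumed. With n = 53 per arm and p̄ the mean of the two rates, power = Φ{[|p₁ − p₂| − z·√(2p̄(1 − p̄)/n)] / √[(p₁(1 − p₁) + p₂(1 − p₂))/n]}. For 5% against 15% at two-sided alpha 0.05: (0.100 − 1.96 × 0.0583) / 0.0575 = −0.25, so power is 40%.

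| Assumed rates | alpha 0.05 | alpha 0.01 |
|---|---|---|
| 5% vs 15% | 40% | 19% |
| 5% vs 20% | 65% | 40% |
| 10% vs 20% | 30% | 13% |

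**The case against.** The strongest reply is that this is one summary sentence in a condensed article. Event definitions, causality fields and form pages usually sit in the full protocol or case report form. The sentence does not contain the word *only*, and *possible* admits suspected reactions. Safety is not a listed aim, and the Abstract claims no more than that evidence may emerge. These points lower the weight of the finding. They do not remove it: the sentence states a rule, and a suspected reaction still needs someone to suspect the treatment first.

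A reader might infer more than the documents support:
- *That there is no control rate at all.* PAAc and NSAAc provide one for attributed reactions, in blinded patients. What is missing is the all-cause rate, and a comparable rate in SOC.
- *That unblinded staff are known to decide causality.* No attributor is named, and the main Discussion points the other way. Its conflict with the sections on randomisation and data collection is a separate blinding question.
- *That no pregnancy outcome is collected.* The epidural item may refer to the current delivery; its time point is unclear. The other birth items may be in the full protocol, so their absence from the article is weak evidence.
- *That serious events can enter only through attribution.* Variables also counts emergency treatment and specialist visits since pain onset, without an attribution condition. Its time points are not given, and a count of contacts does not identify the event.
- *That 5.5% measures the defect.* The bound follows from 53 women and is the same after the fix. A moderate excess could still go undetected with full recording.
- *That obstetric harm is suspected.* Among the needle risks, the article discloses to women only "infection, pain at the puncture site, fainting, bruising", and nothing in it suggests an obstetric effect.

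**Conclusion.** The point holds in a limited form. As written, the recording rule supports a comparison of attributed reactions among VAAc, NSAAc and PAAc. It does not support a statement of safety, or of no significant iatrogenesis, relative to standard care, because it gives no all-cause rate in any arm and no comparable rate in SOC. Unblinded attribution probably adds bias, but its size cannot be calculated from the article. Even with complete recording, about 53 women per arm can exclude only rates above 5.5% (one-sided) or 6.7% (two-sided) when no event is seen. These limits assume that all 53 are followed. The primary pain analysis and the sample size are unaffected.

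The conclusion assumes that the sentence in Variables is the operative rule and that the full protocol does not replace it with all-event recording. The point about birth data is secondary and conditional for the same reason.

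**What to change.** - Reword the sentence in Variables so that all adverse events are recorded in all four arms, by the same question at T1 and T2, whether or not attributed to treatment.
- Keep attribution as a separate field, and state who completes it and whether that person knows the arm.
- Tabulate events by arm, including SOC.
- Where not already collected, take gestational age at delivery, mode of delivery and birth weight from the health record at T3. That visit is already timed from delivery.
- Limit the safety wording in the Abstract and the hypothesis to what about 53 women per arm can exclude.

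The cost is about one form page and slightly more data entry at visits already planned. No extra visit, staff or change to the 212 women is needed. The change gives comparable rates; it does not give power to rule out moderate differences, and the report should say so.

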### Sample size

Taking Wang et al. [31] as a reference, for the primary purpose of the study, namely to compare the change in pain intensity, assessed on an iVAS, between the baseline assessment and the value at 2 weeks after the intervention, a difference of over 20 mm between the VAAc group and the SOC group will be considered statistically significant. For a known standard deviation of 25 mm for each group, a type I (alpha) error of 0.01 and a type II (beta) error of 0.10, 47 patients per group will be required. Including the patients for the PAAc and NSAAc arms, and with an estimated 10% loss to intervention follow-up, a total of 212 patients (53 per group) will need to be assessed.

### Statistical analysis

A descriptive analysis will be performed to assess the comparability of the four groups with regard to baseline demographic information, prognostic variables, and the evaluation of credibility, using measures of central tendency and dispersion for the quantitative variables and frequency distributions for the qualitative ones.

To determine the primary study outcome (change in pain intensity at 2 weeks) and secondary outcomes (change at 2 weeks in functional status with respect to pain, quality of life, and improvement perceived by the patient), a crude analysis will be performed to compare the mean differences between baseline values and at 2 weeks, for the VAAc group and the SOC group, using the Student *t*-test for independent samples or the Mann-Whitney U test if the samples do not present a normal distribution (determined by the Shapiro-Wilk test). Subsequently, simple and multivariate linear regression analyses will be performed, using the same outcome variables, to adjust for unbalanced independent variables, including the treatment group in the first pass, and determining regression coefficients with the corresponding 95% confidence intervals and the coefficient of determination. The main analysis will be by intention-to-treat, but a per protocol analysis will also be performed.

To determine the secondary outcomes of presence of temporary occupational incapacity, reduction in the consumption of analgesic medication at 2 weeks, and presence of pain at 12 and 48 weeks postpartum, the VAAc and SOC groups will be compared, using the χ^2^ test with continuity correction or Fisher’s exact test when the expected values are below 5. Then, simple and multivariate logistic regression models will be obtained, with the same outcome variables, to adjust for unbalanced independent variables, including the treatment group in the first pass, and the relative risk will be determined, with 95% confidence intervals.

Both the quantitative outcome variables (mean differences) and the qualitative ones (difference in proportions) will be expressed with the respective 95% confidence intervals and intention-to-treat analysis criteria will be used (last known value for losses-to-study for the quantitative outcome variables, and penalisation of results in the experimental treatment for the qualitative variables). To assess the specificity of the effect of auricular acupuncture, previous analyses comparing the VAAc treatment group versus PAAc and NSAAc will be repeated. In each test, the bilateral statistical significance limit of *P* <0.01 will established. An intermediate analysis will be performed when complete tracking is concluded for half of the sample population, setting the level of bilateral statistical significance at *P* <0.005, this being a necessary penalisation to minimise type I errors.

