### Randomisation and blinding procedures

The four study arms will be randomised centrally, at the Costa del Sol Hospital, Research Support Unit, to achieve a 1:1:1:1 allocation ratio, stratified by healthcare centre. The health professionals taking part in the study will not be involved in the randomisation process. Patients who meet the inclusion criteria and give their signed informed consent will be included in the study. After inclusion, the researcher will contact the randomisation centre, where the patient’s data will be recorded, and the midwife will be informed, by telephone and by fax, of the patient’s allocation to one of the four study arms. This procedure ensures that randomisation will not be influenced by any of the researchers involved. The patients assigned to the VAAc, NSAAc, and PAAc groups will be blinded with respect to the treatment allocated to them.

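### The primary comparison is a crude change-score test whose form is chosen by a normality test, with adjustment only for variables found unbalanced; one prespecified baseline-adjusted model would be more efficient and would not depend on the data.

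*Protocol article*

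**What the plan says.** The Statistical analysis section of the protocol article takes the primary outcome, change in iVAS at 2 weeks, through two steps.

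- **Crude step.** VAAc and SOC are compared on the mean change from baseline, unadjusted, by Student's t-test "or the Mann-Whitney U test if the samples do not present a normal distribution (determined by the Shapiro-Wilk test").
- **Regression step.** Simple and multivariate linear regressions on the same outcome follow, "to adjust for unbalanced independent variables, including the treatment group in the first pass". No covariate is named in advance.

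Neither baseline iVAS nor centre is named as a model term. Baseline iVAS is measured at T0 (Variables), and randomisation is "stratified by healthcare centre" (Randomisation and blinding procedures) across 21 centres. The section promises mean differences with 95% confidence intervals for quantitative outcomes. It does not say whether the crude or the adjusted result decides the primary question.

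The same section opens with a descriptive comparison of the groups on "baseline demographic information, prognostic variables, and the evaluation of credibility". On credibility, the Variables section says: "Questions 1 and 2 will be assessed after the first treatment session, and questions 3 and 4, after 2 weeks".

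The Sample size section is built on a mean difference: "a difference of over 20 mm between the VAAc group and the SOC group", with an SD of 25 mm per group and "a type I (alpha) error of 0.01 and a type II (beta) error of 0.10, 47 patients per group will be required".

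**The concern.** Three features of the plan work against a clear primary result.

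1. **Efficiency.** A change score subtracts baseline with a coefficient fixed at 1. Analysis of covariance estimates that coefficient and has the smaller residual variance whenever the correlation between baseline and 2-week iVAS is below 1.
2. **Test chosen by the data.** The sample size and the promised interval both concern a difference in means. Mann-Whitney is a rank test of a different quantity. If Shapiro-Wilk triggers the switch, the P value and the reported effect no longer answer the same question.
3. **Covariates chosen by the data.** Which adjusted model is fitted depends on which imbalances happen to appear, so the adjusted estimate cannot be specified beforehand.

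At stake are precision in the main comparison and the ability to say in advance which single number answers the trial's question.

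**Working it through.** **Inputs from the article.** Difference 20 mm; SD 25 mm per group; alpha 0.01, two-sided ("In each test, the bilateral statistical significance limit of" P < 0.01); power 90%; loss 10%; four arms; 21 centres.

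**Assumption.** The correlation rho between baseline and 2-week iVAS is not given; the range 0.3 to 0.7 is used.

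**Step 1: the stated sample size.** n per group = 2 × [25 × (2.576 + 1.282) / 20]² = 46.5, so 47. Allowing for 10% loss, 47 / 0.9 = 52.2, so 53, and 4 × 53 = 212. The article's figures reproduce. Exact (noncentral t) power of the crude t-test with 47 per group is 89.1%; the normal approximation gives 90.4%.

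**Step 2: gain from baseline adjustment.** Let s be the raw-score SD. The change-score variance is 2(1 − rho)s² and the covariance-adjusted variance is (1 − rho²)s². Their ratio is (1 + rho)/2, that is 0.65, 0.75 and 0.85 at rho 0.3, 0.5 and 0.7.

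The Sample size section does not say whether 25 mm is the SD of the change or of the raw score, so both readings are shown. Power is noncentral t, 47 per arm, 20 mm, two-sided 0.01.

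| rho | 25 mm = SD of change: adjusted SD | Crude power | Adjusted power | 25 mm = raw SD: change SD / adjusted SD | Crude power | Adjusted power |
|---|---|---|---|---|---|---|
| 0.3 | 25√0.65 = 20.16 | 89.1% | 98.4% | 29.58 / 23.85 | 74.0% | 92.2% |
| 0.5 | 25√0.75 = 21.65 | 89.1% | 96.6% | 25.00 / 21.65 | 89.1% | 96.6% |
| 0.7 | 25√0.85 = 23.05 | 89.1% | 94.0% | 19.36 / 17.85 | 99.0% | 99.7% |

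**Step 3: behaviour of the planned rules.** This was simulated with 47 per arm, SD of change 25 mm, rho 0.3 and 0.5, with 10,000 null runs and 2,000 runs at 20 mm. A switch meant Shapiro-Wilk below 0.05 in either arm. Imbalance meant a baseline difference at P < 0.05.

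- *Normal errors.* The test switched in about 10% of null trials. Power at rho 0.3 / 0.5 was 90.0% / 89.1% for the Shapiro-Wilk-selected test, 91.7% / 90.2% when adjusting only if baseline was unbalanced, and 98.3% / 96.9% for the fixed adjusted model. Adjustment triggered by imbalance therefore recovers little of the available gain.
- *Strongly skewed (exponential) errors.* The test switched in about 78–90% of trials. Power was 94.0% / 95.0% for the selected test and 97.4% / 95.2% for the fixed model. The advantage over the selected test shrinks here, and at rho 0.5 it is within simulation error.
- *Type I error at nominal 1%, both error shapes.* Selected test 0.9–1.0%, adjust-if-unbalanced 0.6–0.7%, fixed model 0.9–1.1%.

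**The case against.** The strongest defence is that the planned test is legitimate. A change score does use baseline, the comparison is randomised, the test matches the stated outcome, and the trial was sized for it at about 90% power. The analysts are blinded to allocation, and the text sets an order, crude first and regression afterwards. Mean differences with intervals are promised whichever test gives the crude P value. All of this stands, and it limits the point to efficiency and prespecification.

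A reader might infer more in five places, and the article does not support it.

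- **That a switch to Mann-Whitney is likely because VAS is bounded.** With scores clipped to 0–100 under plausible assumed means and SDs, the switch rate was only 7–11%, about the rate with normal data. Marked skew would raise it, but the article gives no distribution.
- **That the switch inflates type I error.** It did not in the simulation.
- **That the trial has two chances to succeed.** If either the crude or the baseline-adjusted result could be claimed, simulated error is 1.6–1.8% against 1%. The article leaves open which result decides, but it nowhere says either may be claimed.
- **That the estimate is biased by adjusting for credibility.** Credibility appears only in a descriptive comparison; nothing makes it a regression covariate.
- **That omitting centre invalidates the test.** Leaving out a stratification factor makes the test conservative. At an assumed intracentre correlation of 0.05 to 0.10, the variance is overstated by 1/(1 − 0.05) − 1 = 5.3% to 1/(1 − 0.10) − 1 = 11.1%.

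**Conclusion.** The point holds as lost efficiency and a data-dependent choice of test and covariates. These are methods that the article itself fixes, not details left to a fuller document. The crude test remains valid.

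The gain in power rests on the assumed correlation and on how the 25 mm is read. It is about 5 to 9 percentage points if 25 mm is the SD of change, and from under 1 to about 18 points if it is the raw-score SD. These figures also assume roughly normal errors. Under strong skew the rank test recovers much of the difference, but the mismatch between rank test and reported mean difference then arises in most trials.

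The argument for one prespecified estimate does not depend on rho.

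**What to change.** State a single primary analysis: a linear model for T2 iVAS on treatment arm, with baseline iVAS as a fixed covariate and a prespecified term for centre. Report the adjusted VAAc–SOC mean difference with its confidence interval whatever Shapiro-Wilk shows, using robust or bootstrap standard errors if residuals are skewed. With baseline in the model, the arm coefficient is the same whether T2 iVAS or the change is the outcome, so the stated endpoint is untouched.

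Fix the form of the centre term in advance. There are about 212 / 21 = 10 women per centre overall, but only about 94 / 21 = 4.5 evaluable women per centre in the primary contrast. A random effect is one reasonable choice.

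Keep the crude test as supportive. Remove selection of covariates by observed imbalance. Limit any further covariates to named pre-randomisation variables; as a precaution this also rules out credibility, which is measured after treatment starts.

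The cost is wording only. The variables are already collected, and 47 evaluable and 53 randomised per group stay as they are. The change should be made before any unblinded comparison, including the planned intermediate analysis.
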